## Abstract

**Introduction:** Overactive bladder (OAB) and urinary incontinence (UI) are prevalent, particularly in older adults, and affect quality of life. OAB involves urgency, frequency, nocturia, and urgency incontinence, often linked to involuntary detrusor contractions. Treatment guidelines recommend a stepwise approach, starting with pelvic floor muscle training (PFMT), followed by pharmacological or minimally invasive therapies, such as neuromodulation. However, the combined effects of PFMT and neuromodulation have not been well established. This study aimed to evaluate the impact of combining pelvic floor exercises with neuromodulation versus PFMT with sham neuromodulation or standard physiotherapy after a 12-week intervention in individuals with OAB and UI. **Methods/Materials:** A double-blind, randomized controlled trial was designed with three groups: PFMT + neuromodulation, PFMT + sham, and conventional physiotherapy (control) in a 1:1:1 ratio. This study followed the CONSORT guidelines and was registered at ClinicalTrials.gov (NCT06783374). The sample size was calculated using GPower^®^ software, assuming a Cohen’s effect size of 1.04, a power of 0.80, an alpha of 0.05, and a 15% dropout rate, totaling 63 participants (21 per group). Participants attended 24 sessions over 12 weeks (2 sessions per week). The interventions were based on previously validated protocols. **Outcomes:** The primary outcomes included health-related quality of life, pelvic floor muscle function, pain, adherence, and general health. The secondary outcomes included Incontinence Quality of Life questionnaire, 3-day bladder diary, International Consultation on Incontinence Questionnaire–Urinary Incontinence Short Form, kinesiophobia, and electromyographic data.

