### 2.4. Procedure

Once the groups have been assigned, four sample collections will take place at the following time points: Pre (baseline), Post_1month_, Post_3months_, Post_6months_ (Figure 2). All the participants will engage in 24 experimental sessions, each with a duration of approximately 60 min. At each assessment point, the studied variables will be monitored and recorded in the “Data Collection Notebook”. It has been created to systematically record both the primary and secondary outcome variables at each measurement point, in alignment with the study protocol.

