## 4. Sample Size

Statistical analysis was performed using a repeated measures analysis of variance (ANOVA), focusing on the primary variable, OAB-q SF. Drawing on a previous study on transcutaneous tibial nerve stimulation in women with idiopathic overactive bladder [26], the Cohen’s effect size was estimated to be 1.04. The statistical power was set at 0.80, with an alpha level of 0.05, considering the three intervention groups. Initially, 54 individuals were allocated to three groups (18 participants per group). To account for a potential 15% dropout rate during follow-up, three additional participants were added to each group, resulting in 21 participants per group and a total sample size of 63. The required sample size was calculated using G*Power software (version 3.1.9.2; Franz Faul, Universität Kiel, Kiel, Germany).

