### 5.2. Primary Outcome

#### The Overactive Bladder Questionnaire-Short Form (OAB-q SF)

The OAB-q SF is a concise, self-administered instrument featuring two scales that evaluate symptom distress and health-related quality of life (HRQoL) in individuals with overactive bladder [38,39]. This condition-specific questionnaire assesses symptom distress using 6 items and health-related quality of life (HRQoL) through 13 items. Patients rate each item on a 6-point Likert scale. The subscale scores are then combined and converted into a scale from 0 to 100. The symptom distress and HRQoL scales are inversely related: a higher symptom distress score reflects more severe symptoms, while a higher HRQoL score signifies better quality of life [25].

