#### 5.3.5. Oxford Scale

The Oxford Scale is a subjective classification system used to assess the strength and quality of PFM contractions through intracavitary palpation with one or two fingers. The modified scale includes 5 grades: 0 = no contraction; 1 = flickering muscle movements; 2 = weak contraction; 3 = increased pressure with slight muscle elevation; 4 = firm contraction with moderate elevation of the vaginal posterior wall; and 5 = strong contraction with finger resistance against the abdominal wall [48].

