## 6. Program Feasibility and Safety: Attendance and Compliance

Adherence to exercise regimens for UI presents a multifaceted challenge, necessitating both behavioral modification and active patient engagement [56]. The process of behavioral change, essential for effective treatment adherence, is often intricate [57]. Empirical evidence indicates that home-based interventions are less efficacious compared to those supervised by a physiotherapist with specialized training [58]. Specifically, a structured exercise program for UI, when supervised during the treatment phase, is associated with higher adherence rates in both the short and long term [59]. Moreover, non-adherence to treatment poses a significant barrier to the success of UI interventions, with the efficacy potentially diminishing substantially if compliance falls below 80% [60]. Consequently, adherence is a critical determinant of the treatment efficacy and the enhancement of quality of life [61]. This study will implement an exercise regimen aimed at enhancing core stabilization and overall strength by incorporating forced exhalation to activate the transverse abdominal muscle, thereby mitigating the adverse effects of increased intra-abdominal pressure. In both the intervention and placebo groups, the training program will be conducted under direct supervision following posterior tibial nerve neuromodulation. Participants in the exercise groups will adhere to the prescribed training frequency, as monitored by the SIRAS scale [59].

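### The abstract names five primary outcomes and the body names one, the OAB-q SF, without saying which of its two opposed scales or which visit is primary.

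*Protocol article*

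**What the plan says.** **Primary outcome.** The abstract says: "The primary outcomes included health-related quality of life, pelvic floor muscle function, pain, adherence, and general health". It does not name the OAB-q SF. Section 4 bases the sample size on a repeated measures ANOVA, "focusing on the primary variable, OAB-q SF", with alpha 0.05 and power 0.80. Section 5.2, headed in the singular, lists that questionnaire alone.

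**The other abstract primaries, as the body treats them.** Pelvic floor muscle function is measured by the Oxford Scale (5.3.5: "The Oxford Scale is a subjective classification system used to assess the strength and quality of PFM contractions") and by EMG (5.3.4), both secondary. The pain-related scale, the Pain Catastrophizing Scale (5.3.7), is also secondary. Adherence appears in section 6: "Participants in the exercise groups will adhere to the prescribed training frequency, as monitored by the SIRAS scale". General health appears only in section 5.1, among the descriptive variables, to detect comorbidities.

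**The instrument.** Section 5.2 describes a 6-item symptom distress scale and a 13-item HRQoL scale. On scoring it says: "The subscale scores are then combined and converted into a scale from 0 to 100". On direction: "The symptom distress and HRQoL scales are inversely related: a higher symptom distress score reflects more severe symptoms", whereas a higher HRQoL score is better.

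**Time.** Section 2.4 says "four sample collections will take place at the following time points": baseline, then 1, 3 and 6 months. The objective at the end of the Introduction concerns the effect after 12 weeks of treatment. Section 10 explains the three later visits without ranking them.

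**Analysis.** Section 8.2.2 plans a mixed time-by-group ANOVA with Tukey's post hoc correction for primary and secondary outcomes alike.

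**The concern.** A stated alpha and power mean something only for an identified test. Here the reader meets two different sets of primary outcomes. Within the set that the body supports, the choices of scale, visit and group comparison are still open. If they are settled after results are seen, a favourable result on any of several measures could be called the primary result, and the 5% error rate would no longer describe the claim.

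The open choice of scale also reaches the randomisation. Section 3 stratifies on baseline OAB-q SF level without naming the scale.

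This is a conflict between parts of one document. It is not a detail that an unseen analysis plan may supply, because the abstract and the body cannot both be right about which outcomes are primary.

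**Working it through.** **1. The plan's own figures.** Inputs from section 4: effect size 1.04, power 0.80, alpha 0.05, three groups, 18 per group, 15% dropout. The dropout step reproduces: 18 × 1.15 = 20.7, rounded up to 21, and 3 × 21 = 63. The starting 54 does not follow from the stated inputs. Reading 1.04 as Cohen's d, one exact two-sided t-test between two groups needs 16 per arm (48 over three arms). The figure 54 appears only with inputs the section does not state. That is a separate question, and nothing below rests on it.

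**2. Abstract against body.**

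| Abstract primary | Place in the body |
|---|---|
| Health-related quality of life | Nearest match is the OAB-q SF (5.2), but the term describes only one of its two scales, and the I-QOL (5.3.1, secondary) also measures it |
| Pelvic floor muscle function | Oxford Scale and EMG, secondary (5.3.5, 5.3.4) |
| Pain | Pain Catastrophizing Scale, secondary (5.3.7); no pain-intensity scale described |
| Adherence | Section 6, monitored in the exercise groups |
| General health | Section 5.1, a descriptive record; no outcome instrument described |

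**3. Family-wise error.** For k independent tests, each at 5%, the chance of at least one false positive is 1 − 0.95^k.

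- k = 1: 5%.
- k = 2 (the two scales): 1 − 0.9025 = 9.8%.
- k = 5 (the abstract's list, one test each): 1 − 0.7738 = 22.6%.

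For two-sided tests with jointly normal statistics, independence gives the maximum, so these are ceilings. Correlations are not in the document. With equal assumed correlations, simulation (400,000 draws) gives:

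| Tests | correlation 0.3 | 0.5 | 0.8 |
|---|---|---|---|
| 2 scales | 9.5% | 9.1% | 7.8% |
| 5 outcomes | 20.9% | 18.3% | 12.6% |

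Tukey's procedure adjusts the three pairwise group comparisons within one outcome. It does not touch the multiplicity across outcomes or scales.

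**4. Cost of splitting alpha instead of choosing.** Assume 1.04 is Cohen's d and applies to every outcome tested. Exact two-sided t-test, n per arm, noncentrality 1.04 × √(n/2), which is 1.04 × 3 = 3.12 at n = 18:

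| Alpha per test | Power, 18 per arm | Power, 21 per arm |
|---|---|---|
| 0.05 (one test) | 85.8% | 90.8% |
| 0.05/2 = 0.025 | 77.7% | 84.7% |
| 0.05/5 = 0.01 | 65.2% | 74.3% |

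**5. Time.** If the clock runs from allocation, the 3-month visit falls at about the end of the 12 weeks. If it ran from the end of treatment, the visits could differ by arm. Section 4.1.3 gives the control arm 8 to 12 sessions at two per week, or 4 to 6 weeks, while the abstract and section 2.4 give all participants 24 sessions, or 12 weeks at two per week. Those passages must be reconciled in their own right. Here they show why the start of the clock has to be written down.

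**The case against.** The strongest reply is that the operative sections agree: sections 4 and 5.2 name one instrument, section 3 stratifies on it, and the alpha and power are attached to it. On that view the only outlier is one sentence in the abstract. This stands in part. The 5% does have a nominal home, and it would be too strong to say that the plan has no primary analysis. It does not settle which scale is meant.

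Four stronger readings are tempting and are not supported:

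- **The two scales are added and improvements cancel.** A reader might infer this from the scoring sentence. But section 5.2 goes on to interpret a high score on each scale separately, which fits summing and rescaling within each scale, as section 5.3.1 describes for the I-QOL. The wording is ambiguous; it does not show a scoring error.
- **Five outcomes at three visits make fifteen tests.** Section 8.2.2 plans one mixed model with time as a factor, not a test per visit. Some of the five, such as general health, have no described measure to compare between arms. For the same reason 22.6% is itself a ceiling.
- **EMG contradicts the abstract.** It does not: the abstract also lists electromyographic data as secondary. The pelvic floor conflict rests on the Oxford Scale.
- **The time point is wholly open.** The 12-week objective and the 3-month visit largely imply it, section 2.4 introduces the visits as following group assignment, and the schedule figures are not shown. It is implied, but it is not designated as primary.

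**Conclusion.** The point holds as an internal contradiction plus an incomplete definition. The abstract and the body disagree on the primary outcomes. The one that the body supports has two opposed scales with neither chosen, and the primary visit is implied but not named. The exposure is at most 22.6% if all five abstract outcomes were tested once each at 5% (12.6% to 20.9% over the assumed correlations), and at most 9.8% for the two scales alone (7.8% to 9.5%). The power figures further assume that 1.04 is Cohen's d and holds for every outcome tested. The documents confirm neither, and they do not say which scale, if either, gave that value.

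**What to change.** 1. Correct the abstract so that the OAB-q SF is the sole primary outcome and all other measures are secondary, matching sections 4 and 5.2.
2. In section 5.2, name one scale as primary, scored 0 to 100 on its own and not merged with the other. If both are to be primary, state how alpha is controlled across them; an even split has the power cost shown above. Name the scale used for stratification in section 3.
3. Name the 3-month assessment, at the end of the 12-week period, as the primary time point, and state that the clock starts at randomisation.
4. In section 8.2.2, state which group comparison or comparisons decide success. The objective names two comparators, sham and conventional physiotherapy, so the choice is the sponsor's, but it must be fixed in advance.

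The cost is wording only. It needs no extra data and, if a single scale is chosen, no additional participants. It should be done before any outcome data are analysed.

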## 1. Introduction

The International Continence Society (ICS) has established the standardized definition of overactive bladder (OAB) syndrome as the presence of urinary urgency, usually accompanied by frequency and nocturia, with or without urgency urinary incontinence, in the absence of urinary tract infections or other obvious pathology. The symptoms of an overactive bladder include four elements: urgency, frequent urination, nighttime urination, and urgent incontinence [1]. Epidemiological data from European countries indicate that the prevalence of overactive bladder (OAB) is higher in women than in men, with 21.9% of women affected. Additionally, OAB is more commonly observed in individuals who are overweight, obese, or aged ≥ 60 years [2]. The symptoms of OAB are caused by involuntary contractions of the detrusor muscle of the bladder during the filling phase of the micturition cycle [3], so urge urinary incontinence (UUI) is widely recognized as a well-known manifestation of OAB [1]. Although OAB is not always linked to detrusor overactivity (DO), as observed in urodynamic studies, it may present either as idiopathic (non-neurological) or as a result of a neurological condition, such as multiple sclerosis or spinal cord injury [4]. OAB can be categorized into two subtypes: “OAB-wet”, which is characterized by urinary incontinence, and “OAB-dry”, which occurs without incontinence [5,6].

The American Urological Association (AUA) clinical guidelines recommend a stepwise approach to the management of overactive bladder (OAB), progressing from less invasive to more invasive treatments based on the patient response [7]. Four primary lines of treatment have been established: noninvasive, pharmacotherapy, minimally invasive, and invasive therapies [8]. Noninvasive therapies primarily focus on incontinence management strategies. Among these, bladder training is strongly recommended for all patients owing to its proven efficacy, as supported by high-quality evidence from systematic reviews, including a Cochrane Review (2023) [9]. Specifically, intentional and focused contraction of the pelvic floor muscles (PFMs) during episodes of urgency, as demonstrated by systematic review findings [10], is maintained until the urgency subsides. Furthermore, multi-joint exercises that incorporate trunk stabilization with abdominal activation have been shown to effectively complement these interventions [11,12]. However, because these studies do not provide the systematization and planning of such interventions, a multidimensional strength training program that includes PFM contraction is needed [13]. Recently, anticipatory postural adjustments of upper and lower limb movements related to PFM have been documented, generated synergistically during involuntary and functional movements [14]. This approach enhances the muscular properties of the striated PFM through reflex responses that promote sensorimotor control of the posture, body awareness, and balance [15].

Due to the promising results, the effect of exercise combined with therapies is highly recommended for patients with persistent symptoms, as it can enhance symptom management and facilitate the appropriate adjustment of treatment based on individual outcomes [16]. Neuromodulation minimally invasive therapies represent effective treatment options for OAB in patients who exhibit inadequate responses to prior interventions or choose to discontinue these approaches. This is supported by a recent network meta-analysis comparing third-line therapies, including botulinum toxin injections, sacral neuromodulation, and percutaneous tibial nerve stimulation (PTNS), which identified these as the most representative and effective techniques [17]. Recently, there has been increased emphasis on the importance of shared decision-making when choosing the most suitable treatment or combination of treatments customized to meet the individual needs of the patient [8]. The combination of different techniques can provide a more comprehensive approach to symptom management in patients with OAB [18]. Previous studies have shown that combining pelvic floor muscle training (PFMT), transcutaneous tibial nerve stimulation, transvaginal electrical stimulation, and motor control exercises offers excellent safety and efficacy, provided that patients maintain long-term adherence to the treatment [8].

Neuromodulatory treatments for OAB and UI are applied at the suprapubic, transvaginal, sacral, and posterior tibial nerve levels [19]. Posterior tibial nerve neuromodulation (PTNN) is a more conservative approach with fewer complications, endorsed by the ICS with a Grade A recommendation internationally [1]. This technique can be performed in two ways: through percutaneous and transcutaneous electrical stimulation of the posterior tibial nerve [20]. It involves retrograde stimulation of pelvic nerves connected to the spinal cord via the sacral plexus in the S2 and S3 segments, where the motor branches of the sacral plexus (parasympathetic fibers) terminate in ganglion cells located in the bladder wall and detrusor muscle [20]. Data indicate that PTNS could lead to significant clinical improvement in patients with OAB with non-obstructive urinary retention [21]. Additionally, it has been observed that neuromodulation can be effective in treating urinary frequency, urgency, and nocturia, and in improving quality of life by around 30% [19]. OAB and UI are highly prevalent conditions that significantly affect quality of life. The efficacy of PFMT and neuromodulation in symptom improvement and urinary continence control is well established. However, the lack of standardized protocols and the need for more comprehensive therapeutic strategies justify further studies to optimize the clinical management of these conditions. Although Firinci et al. [16] conducted a randomized controlled trial supporting the combination of peripheral neuromodulation with PFMT, more protocols seek to improve this by incorporating a longer intervention period and standardized outcome measures, thereby enhancing the methodological rigor and clinical applicability of the findings. Hence, we hypothesized that pelvic floor strength training through a protocol, in combination with prior peripheral neuromodulation, may enhance the ability to inhibit detrusor contractions by utilizing involuntary perineal muscle contractions. The objective of this investigation was to assess the efficacy of combining pelvic floor muscle training with neuromodulation compared to pelvic floor muscle training with sham neuromodulation or conventional physical therapy after a 12-week treatment period in patients diagnosed with OAB and UI. The researchers hypothesized that pelvic floor strengthening, when administered as an adjunct to peripheral neuromodulation, would inhibit detrusor contractions by promoting involuntary contractions of the perineal musculature.

## 2. Materials and Methods

### 2.1. Study Design

This study adopts a prospective, double-blind, randomized controlled trial (RCT) design with a comparative longitudinal approach. The study protocol has been developed following the SPIRIT guidelines, which delineate the essential components that must be incorporated into randomized clinical trial protocols (Figure 1) [22]. The results will be communicated in accordance with the Template for Intervention Description and Replication (TIDieR) checklist to provide a detailed and accurate description of the intervention and its implementation [23].

This double-blind study will include three groups: (i) an exercise program combined with neuromodulation, (ii) an exercise program with a sham neuromodulation procedure, and (iii) a control group receiving conventional physiotherapy treatment, with participants equally distributed among the groups. The Ethics Committee of the Catholic University of Valencia approved the study protocol (13 January 2025) (ID: UCV/-2025/020), and the trial was registered in the ClinicalTrials.gov database under registration number NCT06783374 (20 January 2025). The timetable for completion of the study is as follows: the study will begin on 4 March 2025, with primary completion expected by 10 November 2026. The intervention will be conducted at the Clinics of the Catholic University of Valencia. Prior to the intervention, participants will receive a detailed video briefing that will explain the study’s objectives, procedures, and possible risks. All the participants who agree to participate will provide written informed consent forms prepared in accordance with the ethical principles outlined in the Declaration of Helsinki [24].

### 2.2. Study Population

The study will involve patients diagnosed with UUI and/or OAB who meet specific eligibility criteria, satisfy the clinical standards for PTNN, and are capable of adhering to an exercise regimen. While only one group will receive PTNN, all the participants, irrespective of their assigned groups (exercise + neuromodulation (E_neurom_), exercise + sham (E_sham_), and control group (conventional physiotherapy), must satisfy the same eligibility criteria. Recruitment efforts will include promoting “a new study on urinary incontinence” through flyers and posters distributed throughout Valencia, Spain, as well as through posts on widely used social media platforms, such as LinkedIn, Facebook, and Instagram. Moreover, we plan to implement community outreach, in-person information sessions, and collaboration with local health centers to ensure broader inclusion and improve access for populations. In fact, specialists in gynecology and nephrology play a key role in referring patients who have been diagnosed.

